**Methods/design:**

Key intervention components have been identified from preliminary work (individual and family focus, peer mentoring, technology integration and improved communication and understanding) and are being developed into a pragmatic randomised controlled trial (RCT) supported by recruitment pathways. A steering group of health care professionals and managers will refine the intervention to patient needs. A pilot trial is providing data on intervention implementation, acceptability and feasibility. Twenty youths with type 1 diabetes are being recruited and randomised into an intervention or control group. Physical activity is being measured objectively using the Actigraph GT3X+ monitor at baseline and 1-month follow-up. Contextual factors associated with intervention delivery are being explored.

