### Withdrawal of study participants

The participants will be given every opportunity to clarify points they do not understand and, if necessary, ask for more information. Participants will be given sufficient time to consider the information sheets provided. It will be emphasised that the participant may withdraw their consent to participate at any time without loss of benefits to which they otherwise would be entitled. Participants will only be withdrawn from the study by the researcher if the researcher perceives them to be at risk or if there is a serious adverse event. If there is a serious adverse event (e.g. injury from exercise, medical help sought for diabetes), the details of this will be recorded on a Serious Adverse Event form, provided by the local NHS board and national good clinical practice will be followed. The researchers will monitor any adverse events during the study.

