### Pilot procedures

Participants (child and parent/carer) will be visited a minimum of four times during this pilot study. During visit 1, basic demographic (gender, age), medical information (body mass index, diabetes duration and current therapy), PA and QoL questionnaires (see primary and secondary outcome measures section) will be completed and participants will be given an Actigraph activity monitor and asked to wear this for the next 7 days. An accelerometer wear diary will be given to participants to record attachment and removal.

Visit 2 will occur approximately 8 days later. At this point, activity monitors and wear diaries will be returned and participants will then be randomised into the intervention or control group. At this point, the researcher will open the envelope to reveal the treatment group. Those who have been allocated to the intervention arm of the study will receive the PA consultation and intervention materials. The intervention period will last 4 weeks, after which visit 3 will take place. During this visit, both intervention and control participants will once again be given an Actigraph activity monitor and asked to wear this for the next 7 days. An accelerometer wear diary will again be given to participants to record attachment and removal. Visit 4 will occur approximately 8 days later during which time activity monitors and wear diaries will be returned. Participants will be asked to complete the PA and QoL questionnaires with the researcher. Intervention participants will be invited to participate in a short interview to explore views on the ActivPals intervention programme. At this point, participants in the control group will be offered the physical activity intervention, followed by an interview. A wait list control design will be used as it would be unethical to deny participants’ access to an intervention which we believe is likely to be beneficial to health. See Fig. 3 for study flow chart. More details on the pilot study design are noted below following the PICOT protocol (e.g. Population, Intervention, Comparison group, Outcome measures (feasibility and patient centred) and Timing).

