#### Feasibility outcome measures

We will monitor the feasibility of the trial by tracking recruitment, retention and adherence rates of participants and the most effective points of recruitment. In addition, feedback about the delivery of the intervention, intervention content and perceived impact will all be explored through the qualitative interviews with participants and parents, carried out at the end of the study. The researchers will also meet with the steering group at the end of the study to feedback the results and discuss intervention acceptability.

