We will also determine key process-related outcomes including intervention recruitment, retention and compliance. As mentioned, a qualitative interview will be carried out post-intervention to determine contextual factors associated with delivery of the intervention and to explore patient and health professional experiences of the ActivPals programme including acceptability of procedures, perceived benefits and difficulties. According to the MRC framework [41], qualitative research can be valuable for identifying what the important or ‘active ingredients’ of an intervention are and which elements are not related to the ‘treatment effect’. Topics which will be covered include perceptions of project, sport and PA participation, views on intervention components, attitudes towards PA, benefits and barriers towards PA and sustainability of PA. A parent is encouraged to participate in the interview. With the participant’s permission, the interviews will be recorded and transcribed. Otherwise, notes taken during the interview will be written up in detail as soon as possible afterwards. Interviews will be analysed by thematic analysis. Feasibility and acceptability measures will be reported including programme implementation and fidelity to protocol.

The measures will give an indication of the effects of the intervention on PA levels, sedentary behaviour and quality of life. The acceptability of the measures and missing data will be considered when designing the full-scale trial.

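### The only interview point described for the intervention arm is visit 4 or the end of the study, so the views of children who leave earlier have no described route and interview-based acceptability may be too favourable.

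*Protocol article*

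**What the plan says.** The Pilot procedures section fixes the last trial contact: "Visit 4 will occur approximately 8 days later during which time activity monitors and wear diaries will be returned". Questionnaires are completed at that visit, and the interview sentence follows directly: "Intervention participants will be invited to participate in a short interview to explore views on the ActivPals intervention programme". Controls come later still: "At this point, participants in the control group will be offered the physical activity intervention, followed by an interview".

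The other two accounts of timing agree. Under Feasibility outcome measures, feedback on delivery, content and perceived impact is to be "explored through the qualitative interviews with participants and parents, carried out at the end of the study". Under Patient-centred outcome measures, "a qualitative interview will be carried out post-intervention to determine contextual factors associated with delivery of the intervention".

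On leaving, the section on withdrawal says that "the participant may withdraw their consent to participate at any time without loss of benefits to which they otherwise would be entitled". It also allows the researcher to withdraw a child perceived to be at risk or after a serious adverse event, giving injury from exercise and medical help sought for diabetes as examples of such events. It describes no step for recording a leaver's views or reasons.

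The third phase 2 objective, in the Background, is the acceptability of the recruitment pathways and of the content, delivery, duration and intensity of the intervention, to participants and to health professionals.

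**The concern.** Whether a family is still in the study at visit 4 may depend on how they found the programme or the monitoring. If the interview is offered only then, the informants are selected on something close to what the interview is meant to learn. Children who left because the plan was a burden, or who were withdrawn after an exercise injury, could say most about duration, intensity and difficulties, and they are the ones without a described route.

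At stake is one input to the design of the definitive trial. With about 20 children in all, one or two missing dissenting accounts could be enough for a theme not to appear.

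**Working it through.** The plan states no acceptability rate, threshold or expected dropout, so there is no figure of its own to reproduce. The check is first a comparison of sections, then an illustration on stated assumptions.

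**Who can be reached under the stated timing**

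1. Visit 3 follows the 4-week intervention period, and visit 4 comes about 8 days after visit 3. Visit 4 is therefore about 28 + 8 = 36 days after visit 2, when allocation is revealed and the consultation given.
2. A child who drops the activity plan but stays in follow-up reaches visit 4 and can be interviewed.
3. A child who leaves the study, or is withdrawn by the researcher, within those 36 days does not reach visit 4. None of the three statements of interview timing gives such a child an earlier or separate interview.
4. Control interviews follow the delayed intervention and come from controls still present at visit 4. They cannot supply the views of children who left the intervention arm.

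**How likely it is that someone is missed**

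The abstract gives the total: "Twenty youths with type 1 diabetes are being recruited and randomised into an intervention or control group". The allocation ratio is not stated, so 10 in the intervention arm is an assumption. Let d be the assumed probability that a child leaves before visit 4, independently of the others. The chance of at least one leaver is 1 − (1 − d)^10:

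- d = 5%: 1 − 0.95^10 = 0.40
- d = 10%: 1 − 0.90^10 = 0.65
- d = 20%: 1 − 0.80^10 = 0.89
- d = 30%: 1 − 0.70^10 = 0.97

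**How far the picture could shift**

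Let a_s be the share finding the programme acceptable among those who stay, and a_l the share among leavers. Interviews with stayers alone show a_s. The share in the whole arm is (1 − d)·a_s + d·a_l. The difference is d·(a_s − a_l). Taking a_s = 0.90 as an assumption:

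| d | a_l = 0.90 | a_l = 0.50 | a_l = 0 |
|---|---|---|---|
| 0 | 0 | 0 | 0 |
| 10% | 0 | 0.04 | 0.09 |
| 20% | 0 | 0.08 | 0.18 |
| 30% | 0 | 0.12 | 0.27 |

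For example, at d = 20% and a_l = 0.50, the difference is 0.20 × (0.90 − 0.50) = 0.08. The last column is the extreme in which no leaver found the programme acceptable. None of d, a_s or a_l is given in the document. The interviews are to be analysed thematically, so the study promises no such percentage. The table shows only what drives the selection and that it can be nil.

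**The case against.** The strongest reply is that no completer-only rule is written. The interview sentence sets no condition of finishing the programme, and the other two sections give timing only. How leavers are contacted is the kind of detail that a journal article may leave to the full protocol. This stands in part: nothing bars a leaver from interview, and a reader who infers a stated exclusion goes further than the text. But the article does state the timing, three times and consistently, and an exit interview would have to depart from it. The point concerns that stated timing.

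A reader might also infer that anyone who stops the programme is never asked, or that acceptability is judged by completers alone. Neither is supported. Visit 4 is a trial visit for both arms, so non-adherent children who remain can be interviewed. Consent and randomisation describes consent to the intervention and to the interview as separate, so giving up one need not end the other. Acceptability also draws on parents, health professionals, the steering group, implementation and fidelity. Retention and adherence rates count leavers, so heavy dropout could not be hidden by favourable interviews.

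These sources narrow the gap without closing it. Rates show that children left but not why. The steering group consists of health professionals and managers and meets at the end to receive the results, so it inherits any selection in them. The Feasibility outcome measures section names the interviews as the means of exploring participants' feedback on delivery, content and perceived impact.

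Finally, the article reports recruitment as complete and dates the intervention stage February to April 2016, so interviews at the time of leaving may no longer be possible. That affects which part of the remedy can still be used.

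**Conclusion.** The point holds in a limited form. For intervention-arm children who leave the study before visit 4, including any withdrawn after a serious adverse event, the plan describes no route to their views. The participant interviews may therefore give too favourable an account of acceptability.

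It would be wrong to conclude that the result will be biased upwards. There is no bias if nobody leaves or if leavers think as stayers do, and its size cannot be fixed from the document. Under the assumptions in the working (10 children in the arm, 90% approval among stayers), it runs from 0 to 0.09 at 10% loss and from 0 to 0.18 at 20%. Those figures are illustrations, not estimates. The defect is modest and does not touch the accelerometer or quality-of-life outcomes, but it bears directly on a stated objective and is cheap to repair.

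**What to change.** Amend Pilot procedures, Feasibility outcome measures and Patient-centred outcome measures so that the optional interview, under its separate consent, is offered to every child randomised to the intervention and their parent. For those who leave early, offer it at or soon after leaving, by phone if preferred. The same independent MSc student named under Limitations of the research would conduct it, and no one would be pressed for reasons.

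Report the number interviewed out of all randomised to the intervention, split by whether they reached visit 4, and read the themes alongside retention and adherence. With so few children the split is there to show who was heard, not to compare groups.

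If visits are already finished, report that denominator, state the limitation and carry the exit interview into the definitive trial.

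The cost is a few short extra calls by an interviewer already in place. Some leavers will decline, so the gap will shrink but may not disappear.

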#### Population

See the ‘Study population’ section.

#### Intervention

The ActivPals intervention programme will be developed during phase 1.

#### Comparison group

The comparison group will receive standard diabetes care. Control participants will be offered the intervention after they have completed follow-up outcome measures.

#### Feasibility outcome measures

We will monitor the feasibility of the trial by tracking recruitment, retention and adherence rates of participants and the most effective points of recruitment. In addition, feedback about the delivery of the intervention, intervention content and perceived impact will all be explored through the qualitative interviews with participants and parents, carried out at the end of the study. The researchers will also meet with the steering group at the end of the study to feedback the results and discuss intervention acceptability.

#### Patient-centred outcome measures

Objective measures of physical activity and sedentary behaviour will be collected using the Actigraph GT3X+ monitor. This monitor will allow objective recording of daily time spent in sedentary, light and moderate to vigorous physical activity. These monitors are small (approx size of a 2-pound coin) and lightweight (19 g). Participants will be asked to wear the accelerometers around the waist during waking hours for 7 days, excluding water-based activities. Accelerometer data will be downloaded to Actilife software (version 6.4.3). In line with previous studies, a minimum wear time for a valid day will be defined as 6 h/day, with 3 days of data required for analysis inclusion [33, 34].

The primary outcome measure of daily time spent in MVPA and sedentary behaviour will be determined using cut-points calibrated and validated in paediatric studies: sedentary (<100 cpm) [35] and MVPA (≥3200 cpm) [36]. In addition to the accelerometer data, information will be gathered about the type, frequency and location (e.g. school) of activities undertaken in the last 7 days. This information will be collected from participants with the help of their parent/cares at baseline and follow-up (post-intervention/control). This questionnaire will be developed based on the findings of a previously conducted survey study [37].

Generic and disease-specific questionnaires will be used to measure quality of life in participants. The PedsQoL 4.0 Generic Core Scale was used to measure general quality of life [38]. This 23-item questionnaire contains the following subscales: physical functioning, emotional functioning, social functioning and school functioning. A psychosocial health summary score will be calculated from the average of the emotional, social and school functioning subscales, a physical health summary score (from the physical functioning subscale) and a total overall score from the average of all subscales. This scale has shown good reliability and validity in this population [38, 39]. The PedsQoL 3.0 type 1 Diabetes Module is a 28-item questionnaire measuring diabetes-specific QoL consists of five subscales: diabetes symptoms, treatment barriers, treatment adherence, worry and communication. Patients (self-report) and their parents (proxy-report of the child’s QoL) will complete questionnaires by rating items on how much each was a problem in the previous month using a 5-point Likert scale (‘0’ = never a problem; ‘4’ = almost always a problem). This questionnaire has been validated and has shown to be reliable in children with type 1 diabetes [38, 40]. Changes in general QoL and diabetes module scores will be analysed between intervention and control groups to asses for any trends in intervention effects.

We will also determine key process-related outcomes including intervention recruitment, retention and compliance. As mentioned, a qualitative interview will be carried out post-intervention to determine contextual factors associated with delivery of the intervention and to explore patient and health professional experiences of the ActivPals programme including acceptability of procedures, perceived benefits and difficulties. According to the MRC framework [41], qualitative research can be valuable for identifying what the important or ‘active ingredients’ of an intervention are and which elements are not related to the ‘treatment effect’. Topics which will be covered include perceptions of project, sport and PA participation, views on intervention components, attitudes towards PA, benefits and barriers towards PA and sustainability of PA. A parent is encouraged to participate in the interview. With the participant’s permission, the interviews will be recorded and transcribed. Otherwise, notes taken during the interview will be written up in detail as soon as possible afterwards. Interviews will be analysed by thematic analysis. Feasibility and acceptability measures will be reported including programme implementation and fidelity to protocol.

The measures will give an indication of the effects of the intervention on PA levels, sedentary behaviour and quality of life. The acceptability of the measures and missing data will be considered when designing the full-scale trial.

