There is now a small body of evidence which suggests regular physical activity (PA) can significantly reduce HbA1c levels in individuals with type 1 diabetes [7, 10, 11]. This builds on the prolific evidence showing the positive physical and psychological benefits of regular PA in childhood and adolescence [12]. Regular physical activity is therefore recommended in clinical guidelines as one of the core elements of good type 1 diabetes management [13]. Despite appreciation for the benefits of physical activity, evidence suggests youths with type 1 diabetes are less physically active than peers without diabetes [14–16]. For example, a recent study [16] found that young people with type 1 diabetes aged 7–9 and 12–14 years spent on average 78 % (10.2 h/day) of the waking day sedentary and 43 min/day participating in moderate to vigorous PA. Sedentary behaviour is a distinct class of behaviours (i.e. sitting, watching television, playing video games) that is characterised by little physical movement and low energy expenditure [17]. Only two of the 40 participants in the study achieved minimum guidelines of PA participation of 60 min moderate to vigorous intensity PA (MVPA) on each accelerometer wear day, and 19/40 did not achieve 60 min of MVPA on any day. As PA levels are well below the recommendations for health and sedentary behaviour is high in youths with type 1 diabetes, there is clearly a need for intervention studies to support this population to lead an active lifestyle.

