### Statistics and data analysis

Descriptive statistics will be presented (mean and standard deviation) with 95 % confidence intervals presented for each group separately. Changes in physical activity and QoL from baseline and follow-up will be assessed using an ANOVA. As this is a feasibility and pilot study, the study will be underpowered; therefore, quantitative outcomes will be interpreted only as feasibility and pilot data.

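### The primary outcome is absolute daily sedentary and MVPA time from days with as little as 6 h of wear, so a difference in wear between arms or visits can look like a change in behaviour

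*Protocol article*

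**What the plan says.** Under Patient-centred outcome measures, the protocol article fixes three things.

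- The scale: "The primary outcome measure of daily time spent in MVPA and sedentary behaviour will be determined using cut-points calibrated and validated in paediatric studies". The outcome is time per day; it is not stated as a share of the time worn.
- The wear instruction: "Participants will be asked to wear the accelerometers around the waist during waking hours for 7 days, excluding water-based activities".
- The validity rule: "a minimum wear time for a valid day will be defined as 6 h/day, with 3 days of data required for analysis inclusion". No type of day is specified.

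Under Statistics and data analysis: "Changes in physical activity and QoL from baseline and follow-up will be assessed using an ANOVA". Wear time does not appear there. Pilot procedures says that wear diaries record when the monitor goes on and comes off, but gives them no role in the analysis.

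The Background gives levels from an earlier study of young people with type 1 diabetes, who "spent on average 78 % (10.2 h/day) of the waking day sedentary and 43 min/day participating in moderate to vigorous PA". That study's sedentary time is reported both as a percentage and in hours; the trial's own outcome is given only as time.

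**The concern.** Minutes recorded by an accelerometer depend on behaviour and on how long the monitor was worn. With a floor of 6 h, two valid days can differ greatly in length, and a 6 h day cannot record more than 360 sedentary minutes whatever the child did.

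Baseline monitoring ends before the allocation envelope is opened, so baseline wear should differ between arms only by chance. Follow-up monitoring is different. It comes straight after four weeks in which only the intervention arm has had a wearable self-monitoring device and continuing contact from the researcher, who is unblinded and also collects the data. Monitor-wearing habits could diverge at that point, in either direction. With 20 participants, chance imbalance is a further route. A difference between visits would likewise affect any within-group change.

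At stake are the preliminary estimates of effect on activity and sedentary behaviour listed among the Phase 2 objectives, which Strengths of the research calls important for the definitive trial. The intervention aims to raise MVPA and lower sedentary time. Longer wear raises both and shorter wear lowers both, so a wear difference flatters one measure and penalises the other.

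**Working it through.** The article states no SD, effect size, alpha or power, so there is no figure of its own to reproduce. The check uses its Background values.

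**Inputs.** Sedentary time 10.2 h/day, equal to 78% of the waking day; MVPA 43 min/day (Background). Valid-day floor 6 h (Patient-centred outcome measures). Total sample 20 (Abstract).

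**Step 1: implied waking day.** 10.2 / 0.78 = 13.1 h (12.9 to 13.2 h allowing for rounding of both inputs). A 6 h day covers 6 / 13.08 = 46% of it.

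**Step 2: minutes per hour worn**, assuming that unworn time has the same activity mix as worn time.

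- Sedentary: 0.78 × 60 = 46.8 min per hour.
- MVPA: 43 / 13.08 = 3.3 min per hour, or 5.5% of wear.

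**Step 3: the same behaviour at different wear.**

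| Wear | Sedentary (min) | MVPA (min) |
|---|---|---|
| 6 h | 281 | 19.7 |
| 10 h | 468 | 32.9 |
| 13.1 h | 612 | 43.0 |

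Between the first and last rows the gap is 331 min sedentary and 23 min MVPA. These are the extremes that the rule permits, not an expected contrast.

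**Step 4: effect of a difference in mean wear.** For a between-arm comparison of change, what counts is the difference between arms in the change in wear; a gap that is equal at both visits cancels.

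- 1 h: 46.8 min sedentary and 3.3 min MVPA, each 1 / 13.08 = 7.6% of the full-day value.
- 2 h: 93.6 min sedentary and 6.6 min MVPA.
- If the lost hour is 50 to 100% sedentary instead of 78%, the 1 h sedentary shift is 30 to 60 min.

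**Step 5: could this be read as an effect?** Assume 10 per arm (the article does not state the ratio), a two-sided 5% test, and SDs of change that are also assumptions. Under the normal approximation the probability is Φ(shift / (SD × √(2/10)) − 1.96).

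| Measure | Assumed SD of change (min) | 1 h | 2 h |
|---|---|---|---|
| Sedentary | 60 / 90 / 120 | 0.42 / 0.21 / 0.14 | 0.94 / 0.64 / 0.42 |
| MVPA | 10 / 15 / 20 | 0.11 / 0.07 / 0.06 | 0.31 / 0.16 / 0.11 |

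A t-test with 18 degrees of freedom gives slightly lower values for sedentary time (0.38 / 0.20 / 0.13 at 1 h). The artefact can be material for sedentary time. For MVPA a 1 h difference hardly exceeds the nominal 5%.

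**Step 6: on a percentage scale.** Under the same assumption the child in Step 3 scores 78% sedentary and 5.5% MVPA at every wear length, so the artefact is zero. If lost hours have a different mix, some bias remains.

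**The case against.** The strongest reply is that this is a condensed article with a very short statistics section. A wear-time covariate could sit in an analysis plan that is not shown, and nothing in the article rules one out. That stands as far as the covariate goes, and its absence alone would be no finding. But the article does fix the outcome scale and the validity rule, and it is their combination that lets recorded minutes follow wear.

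Several further points stand and limit the concern.

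- The 6 h/3-day rule is supported by cited studies. It is not wrong in itself.
- Both arms get the same monitor, instruction, diary and visits. A reader might infer that bias will occur; the documents show only that it can.
- Participants are asked to wear the monitor throughout waking hours, so mean wear may lie well above the floor.
- A reader might infer that a school-day baseline could be set against an all-weekend follow-up. A 7-day window holds two weekend days and three valid days are needed, so it cannot. The weekday/weekend mix can still differ.
- A reader might infer that an SD inflated by wear is handed to the definitive trial. No passage says that an SD is carried forward. The article also differs on the source of the effect size: the Phase 2 objectives place its estimation after the pilot evidence, while the section on Phase 2 bases it on previous literature.
- The statistics section limits the quantitative results to feasibility and pilot use.

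**Conclusion.** The point holds, at moderate weight. As written, the primary measures scale with wear, at about 47 min/day sedentary (30 to 60) and about 3 min/day MVPA per hour of difference. Sedentary time is where this matters; the MVPA shift is equal in proportion but small in minutes.

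The size rests on the Background averages applying to this sample and on unworn time resembling worn time, with the range showing departures from that for sedentary time. The probabilities in Step 5 also rest on assumed SDs and equal allocation. The bias arises only if wear differs between arms or visits, which is plausible here but not documented.

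A reader might take this as a defect that invalidates the pilot. The documents do not support that: recruitment, retention, adherence and acceptability do not depend on the outcome scale, and the effect data are declared to be pilot data. What is weakened is the preliminary evidence of effect, mainly on sedentary behaviour.

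**What to change.** Keep the 6 h/3-day rule. Define sedentary time and MVPA as a percentage of wear time, or analyse minutes with mean daily wear time as an adjustment. Report wear time and the weekday/weekend mix by arm and visit, so that any imbalance is visible. A sensitivity analysis restricted to longer days, for example at least 10 h, is optional.

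Recruitment is complete, but this needs no new data, because wear can be taken from the monitor files and the diaries. The percentage scale uses no extra degrees of freedom but is less direct than minutes, notably against the 60 min MVPA guideline; minutes can be shown alongside. The covariate route keeps minutes and costs one extra term in a 20-person analysis. Neither removes bias if unworn hours differ in kind from worn ones. The choice should be recorded before the outcome data are analysed.
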